## Abstract

**Background:** The CRASH-3 trial is a randomised trial on the effect of tranexamic acid (TXA) versus placebo on death and disability in traumatic brain injury (TBI). The CRASH-3 intracranial bleeding mechanistic study (IBMS) is a randomised trial nested within the CRASH-3 trial to examine the effect of TXA versus placebo on intracranial bleeding and infarction.

**Methods:** Patients eligible for the CRASH-3 trial, with a GCS of 12 or less or intracranial bleeding on a pre-randomisation CT scan are eligible for the IBMS. The occurrence of intracranial bleeding, infarction, haemorrhagic oedematous lesions, mass effect and haemorrhage evacuation is examined within 28 days of randomisation using routinely collected brain scans. The primary outcome is the volume of intra-parenchymal bleeding in patients randomised within three hours of injury (adjusted for prognostic covariates). Secondary outcomes include a composite “poor” outcome, progressive and new intracranial bleeding, intracranial bleeding after neurosurgery and cerebral infarcts seen up to 28 days post-randomisation. All outcomes will be compared between treatment groups.

**Statistical analyses:** The primary outcome will be analysed using a covariate adjusted linear mixed model. The same analysis will be done separately for patients who undergo haemorrhage evacuation post-randomisation. We will express the effect of TXA on the composite outcome, new and progressive bleeding using relative risks and 95% CIs, and on cerebral infarcts using hazard ratios and 95% CIs. We will conduct sensitivity analyses assuming missing data are MCAR or MNAR.

**Conclusion**: The IBMS will provide information on the mechanism of action of TXA in TBI. This pre-specified statistical analysis plan is a technical extension of the published protocol.

**Trial registration: **The CRASH-3 trial was prospectively registered at the
International Standard Randomised Controlled Trials registry (19 July 2011) and
ClinicalTrials.gov (25 July 2011). The registries were updated with details for the IBMS on 20 December 2016.

## Introduction

Worldwide over 50 million people experience traumatic brain injury (TBI) every year
^1^. TBI is the leading cause of death and disability in young adults
^2^, particularly in low-income and middle-income countries where rates of road traffic crashes are increasing
^3^. Falls are the most frequent cause of TBI in high-income countries
^4^. Intracranial bleeding is common after TBI, mostly in the first few hours after injury
^5^. The larger the bleed the greater the risk of death and long-term disability
^6^. To improve outcome from this life threatening and potentially disabling condition, effective treatments are needed to reduce intracranial haemorrhage expansion.

The permeability of the blood-brain barrier is compromised after TBI
^7^. Tranexamic acid could penetrate the blood-brain-barrier to enter the cerebrospinal fluid
^8,
9^, inhibit the enzymatic breakdown of fibrin blood clots and reduce intracranial haemorrhage expansion. A recent systematic review identified two completed randomised trials of tranexamic acid in TBI
^10^. When the two trials were combined in a meta-analysis (n=478), there appears to be a statistically significant reduction in intracranial haemorrhage growth (RR 0.75, 95% CI 0.58–0.98; P = 0.03) and mortality (RR 0.63, 95% CI 0.40–0.99; P = 0.05) with tranexamic acid. Neither trial found evidence for an increased risk of infarction with tranexamic acid (RR 0.51, 95% CI 0.20–1.32; P = 0.17)
^11^ (0 infarcts – tranexamic acid group, 3 infarcts – placebo group)
^12^. However, the confidence intervals are wide and the quality of this evidence is low. Therefore, the effect of tranexamic acid on mortality, intracranial bleeding and infarction in TBI remains uncertain.

The CRASH-3 trial, with a planned sample size of 13,000 patients, will be the largest randomised trial into the effect of tranexamic acid in isolated TBI
^13^. The CRASH-3 trial is a prospective, international, multi-centre, parallel group, placebo-controlled randomised trial that examines the effects of tranexamic acid on death and disability in TBI. Patients who are within 8 hours of their TBI and have intracranial bleeding on a computed tomography (CT) scan or a Glasgow Coma Score (GCS) of 12 or less, and no significant extra-cranial bleeding, are potentially eligible for inclusion in the CRASH-3 trial. The original 8 hour time window for recruitment was restricted to 3 hours of injury in 2016 in order to reliably examine the effect of tranexamic acid given soon after injury. Eligible patients are randomly allocated (1:1) to receive tranexamic acid or matching placebo (0.9% sodium chloride). The 1 gram loading dose of the trial treatment is administered by intravenous injection within minutes of randomisation in hospital. The 1 gram maintenance dose is administered by intravenous infusion as soon as the loading dose has completed. Tranexamic acid or placebo are given as an additional treatment to the routine management of TBI. The aims and methods for the CRASH-3 trial are presented in detail elsewhere
^13^.

The CRASH-3 trial is based on the premise that intracranial bleeding contributes to head injury death and disability in patients with TBI. By inhibiting fibrinolysis, tranexamic acid is expected to reduce the extent of intracranial bleeding
^14^. Therefore, we expect to see less intracranial bleeding in head CT scans of patients treated with tranexamic acid, particularly in those treated soon after injury when the risk of haemorrhage expansion is greatest
^5^. On the other hand, tranexamic acid might increase the risk of cerebral thrombosis and infarction in TBI patients, potentially worsening neurological outcome
^15–
17^. In this case, we expect to see more infarcts in patients treated with tranexamic acid, particularly in those treated after a prolonged period after injury when there is an increased risk of thrombotic disseminated intravascular coagulation
^15^.

The CRASH-3 Intracranial Bleeding Mechanistic Study (IBMS) is a randomised trial nested within the CRASH-3 trial and examines the effect of tranexamic acid on intracranial bleeding and infarction (protocol version 1.3 currently in use)
^18^. The IBMS evaluates the effect of tranexamic acid on bleeding expansion using a validated method (ABC/2)
^19^ to measure the total bleeding volume on routinely collected CT scans done soon after randomisation. The blinded data from ≈1,000 patients in the IBMS so far suggests that this scan is done within a mean of 44 hours after randomisation. Bleeding is well visualised on CT in the early stage of injury
^20^. Because infarction takes longer to manifest on CT imaging
^21^, the effect of tranexamic acid on infarction is examined using all routinely collected brain imaging (including magnetic resonance imaging) done within 28 days of randomisation. The IBMS will provide information on the mechanism of action of tranexamic acid in TBI and could facilitate the generalisation of trial results
^22^. This pre-specified statistical analysis plan is a technical extension of the published protocol
^19^.

## Trial methods

The aims and methods for the IBMS are presented in detail elsewhere
^18^.

### Aim

The IBMS aims to examine the mechanism by which tranexamic acid exerts its effects in patients with isolated TBI. Specifically, we will assess the effect of tranexamic acid on intracranial bleeding and infarction.

### Trial design and eligibility criteria

The IBMS is a randomised, placebo-controlled, parallel group, international, multi-centre, double-blind trial nested within the CRASH-3 trial. Patients who fulfil the eligibility criteria for the CRASH-3 trial, with a GCS of 12 or less or intracranial bleeding on a CT scan done before randomisation, are eligible for inclusion in the IBMS.

### Trial registration

The CRASH-3 trial was prospectively registered at the International Standard Randomised Controlled Trials registry (
ISRCTN15088122) on 19 July 2011, and ClinicalTrials.gov on 25 July 2011 (
NCT01402882). The registries were updated with details for the IBMS on 20 December 2016.

### Ethical approval

The UK Medical Research and Ethics Committee and Health Research Authority reviewed the protocol and supporting documents for the IBMS and provided a favourable ethical opinion on 8 June 2016 (Research Ethics Committee Reference 12/EE/0274). All participating UK hospitals have provided Research and Development approvals and letters of access for the IBMS to be conducted at their respective sites. The Malaysian Medical Research and Ethics Committee reviewed the protocol and supporting documents for the IBMS and provided favourable ethical opinion on 16 May 2017 (Reference (25) KKM/NIHSEC/P12-476). All relevant national and local ethical approvals will be gained from additional sites. Favourable ethical opinion was received from the Observational/Interventions Research Ethics Committee at LSHTM on 24 May 2016 (Reference 11535). The relevant Medical Research and Ethics Committees will review important protocol modifications for approval before implementation, and registries updated as appropriate.

### Consent to participate

TBI patients are physically and mentally incapable of providing informed consent to participate in a clinical trial. As acknowledged in the Declaration of Helsinki, patients who are incapable of giving consent are an exception to the general rule of informed consent in clinical trials
^23^. In the CRASH-3 trial, patients are unable to provide consent and so consent is sought from the patient’s relative, legal representative or the responsible clinician. If and when the patient regains capacity to provide informed consent, they are informed about the trial and written consent sought to continue their participation in the trial. If a patient or patient representative declines consent, they are withdrawn from the trial. For patients who were included in the trial but did not regain capacity, written informed consent is sought from a relative or legal representative. Written informed consent from patients, their relatives, legal representatives or the responsible clinician includes consent for the publication of anonymised patient data. The requirements of relevant local and national ethics committees are adhered to at all times.

The CRASH-3 trial includes consent to extract data from patient medical records. Collecting brain imaging data for the IBMS is consistent with the consent procedure used in the CRASH-3 trial. It would be impractical to re-consent patients or relatives/legal representatives to brain imaging, particularly for patients who have deceased or are disabled as a result of their injuries where re-consent would be distressing and unwelcome. The LSHTM and national Ethics Committees extended their approvals to extract brain imaging data from CRASH-3 trial patients without further patient consent. Patients who withdrew from the main CRASH-3 trial would not be included in the IBMS.

### Participating hospitals

The hospitals participating in the IBMS were selected based on the number of patients enrolled in the CRASH-3 trial, the availability of electronic imaging at site and the willingness of the trial principal investigator at site to take part. We invited ten of the highest recruiting CRASH-3 trial hospitals in the United Kingdom (UK) to take part (Queen Elizabeth Hospital, Birmingham; Royal London Hospital; University Hospital Coventry; Salford Royal Hospital; St George’s Hospital, London; King’s College Hospital, London; St Mary’s Hospital, London; Addenbrooke’s Hospital, Cambridge; John Radcliffe Hospital, Oxford, Southmead Hospital, North Bristol). We also invited four hospitals in Malaysia to take part: Hospital Sungai Buloh, Penang General Hospital, Hospital Sultanah Nur Zahirah and Hospital Sultanah Bahiyah. We will report all participating sites in the final results publication.

### Sample size

We originally planned for the IBMS to be conducted in 1,000 CRASH-3 trial patients. This sample size was based on the reduction in bleeding volume seen with tranexamic acid in the CRASH-2 Intracranial Bleeding Sub-study (Perel
*et al.,* 2012). We expected a 15% reduction in intracranial bleeding with tranexamic acid (24ml tranexamic acid, 28ml placebo), a correlation of 0.6 between pre- and post-randomisation bleeding volumes, and a standard deviation of 28ml. This gave an unadjusted sample size estimate of 1542, which was reduced to 987 with adjustment (1542*(1-(0.6
^2^)) (Borm, 2007). 

Due to the large amount of missing data (only around half of patients are scanned both pre-randomisation and post-randomisation), we increased the sample size for the CRASH-3 IBMS to include around 1700 patients. This was the approximate maximum number of patients the scan assessor could feasibly collect data from before the CRASH-3 trial completed recruitment. Using the same expected treatment effect, standard deviation, correlation and baseline adjustment values as the original sample size calculation, this increased power to 95%. (at alpha=0.05) However, this calculation is not adjusted for missing data. If we assume that 47% of patients will be dropped from the analyses, this leaves a study with 901 patients scanned both pre-randomisation and post-randomisation. Using the same standard deviation (adjusted for baseline), correlation and baseline adjustment values as the original sample size calculation, a study with 901 patients would have 76% power to detect the expected treatment effect.

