### Primary outcome

The mean volume of intra-parenchymal bleeding will be compared between trial arms in patients randomised within three hours of injury, adjusting for prognostic covariates.

In the original IMBS protocol
^18^, we said the total volume of intracranial bleeding would be compared between treatment groups. Since publishing the protocol, we have collected blinded data from 1700 trial patients, which suggest that any effect of tranexamic acid on intracranial bleeding expansion may only be reliably detected in intra-parenchymal bleeds. Intra-parenchymal bleeds are less likely to be surgically evacuated compared to subdural and epidural bleeds, which are often larger and therefore substantially increase intracranial pressure and require urgent neurosurgical evacuation. Large subdural and epidural bleeds are easier to evacuate because they occur outside of the brain tissue, whereas intra-parenchymal bleeds often occur deep within the brain tissue so it is difficult to evacuate them without causing further harm. Therefore, we may not be able to reliably examine the effect of tranexamic acid on subdural and epidural bleed expansion given that large bleeds are often evacuated before we can examine any effect of tranexamic acid on them. Including bleeds that may not be affected by tranexamic acid in the primary outcome would dilute any effect of tranexamic acid on intracranial bleeding expansion to the null. Furthermore, when excluding patients who have undergone neurosurgery by the first rated post-randomisation scan, the proportional expansion of intra-parenchymal bleeding from pre- to post-randomisation is greater than for all other types of intracranial bleeding. Indeed, a recent randomised trial found a statistically significant reduction in intracerebral bleeding expansion with tranexamic acid
^24^. Finally, intra-parenchymal bleeds are often spherical in shape, so there is less measurement error with the ABC/2 method of volume estimation compared to subdural and epidural bleeds, which have concave and convex shapes, respectively. For these reasons, the primary outcome will examine the effect of tranexamic acid on the total volume of intra-parenchymal bleeding.

In the original IBMS protocol

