The blinded data indicates that pre-randomisation and post-randomisation bleeding volumes are positively skewed. Because bleeding volumes are skewed, this data will be log transformed before entered into the linear mixed model. The anti-log of the treatment effect estimate and its corresponding 95% CIs will be presented to aid interpretation. The treatment effect estimates will provide an estimate of the relative increase or decrease in haemorrhage volume with tranexamic acid.

In the original protocol, we planned to analyse the primary outcome using ANCOVA. Since publishing the protocol, we learnt that less than 50% of patients were scanned both pre- and post-randomisation. Because the pre-randomisation mean bleeding volume of the observed data may be different from the true pre-randomisation mean bleeding volume, the estimates from the ANCOVA model may be biased. Compared to ANCOVA, linear mixed models are more powerful and typically less biased when there are missing data
^26^.

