## Conclusion

This statistical analysis plan updates our previously published protocol
^18^. The main changes are: an increased sample size from 1,000 to a maximum of 2,000 patients, a comparison of intra-parenchymal bleeding expansion between treatment groups for the primary outcome, the use of covariate adjusted linear mixed models for the primary analysis and relevant secondary analyses, and restriction of the analysis of the primary and secondary outcomes (new and progressive bleeding) to patients treated within three hours of injury. We present our plan for the statistical analyses in advance of the database lock and un-blinding to guard against data dependent analyses. The CRASH-3 IBMS should provide reliable evidence on the effect of tranexamic acid on intracranial bleeding and infarction in TBI.

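### The 95% and 76% power figures describe the superseded primary analysis; the SAP gives no power for the current one

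*SAP article*

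**What the plan says.** **Sample size.** The expected effect is 24 ml with tranexamic acid against 28 ml with placebo, with "a correlation of 0.6 between pre- and post-randomisation bleeding volumes, and a standard deviation of 28ml". These inputs led to 1542 patients before adjustment for baseline volume and 987 after it. The target was then raised to around 1700, for which 95% power is given with the same effect, SD and correlation. Allowing for 47% of patients to drop out of the analysis leaves 901, and "a study with 901 patients would have 76% power to detect the expected treatment effect".

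**Primary outcome.** "The mean volume of intra-parenchymal bleeding will be compared between trial arms in patients randomised within three hours of injury". The same section explains that the protocol had used total intracranial volume in everyone randomised up to 8 hours after injury.

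**Primary analysis.** Volumes are log-transformed and the effect is reported as a ratio. ANCOVA is replaced by a linear mixed model that includes patients with only one of the two scans, adjusted for time to scan, GCS, age, systolic pressure and site. The stated reason for leaving ANCOVA is that "we learnt that less than 50% of patients were scanned both pre- and post-randomisation".

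**Conclusion.** The changes listed include "an increased sample size from 1,000 to a maximum of 2,000 patients", along with the new outcome, model and time window. No section restates the effect, SD, correlation, number of patients or power for the new primary analysis.

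**The concern.** The Sample size section was revised for the larger sample and the missing scans, but not for the change of outcome, population and scale. An SD of 28 ml is not an input to a model fitted to log volumes. Nor can all 901 twice-scanned patients be assumed to enter an analysis limited to 3 hours: the Subgroup analyses section keeps a stratum of more than 3 to 8 hours, so some enrolled patients fall outside it. The 47% taken as dropped also does not describe a model that retains patients with one scan.

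This is the only power statement in the SAP. If the primary result is null, readers will judge how informative it is against a figure that was never calculated for that test. The estimate and its confidence interval are unaffected.

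**Working it through.** **Inputs from the Sample size section.** Difference 4 ml (28 − 24); SD 28 ml; correlation 0.6; alpha 0.05, taken as two-sided; 1:1 allocation (Introduction).

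**1. Reproducing the SAP's figures.**
- Unadjusted size per arm for 80% power: 2 × (1.96 + 0.8416)² × 28² / 4² = 769.2, so 1540 in total. A t-based calculation gives 770.15, rounded up to 771 per arm, or 1542 as stated.
- Baseline adjustment: 1542 × (1 − 0.6²) = 986.9, stated as 987.
- Adjusted SD: 28 × √(1 − 0.36) = 22.4 ml.
- Power = Φ(difference / SE − 1.96), with SE = SD × √(4/N).
- N = 1700: SE 1.087, 4/SE = 3.681, power 95.7% (stated 95%).
- 1700 × 0.53 = 901: SE 1.492, 4/SE = 2.680, power 76.4% (stated 76%).

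The arithmetic is sound for the superseded design.

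**2. The paired share.** 901/1700 = 53%, whereas the Primary analysis section says fewer than half had both scans. Half of 1700 is 850: SE 1.537, 4/SE = 2.603, power 74.0%. The SAP's own formula therefore gives less than 74%, even for the old outcome.

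**3. What changed.**

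| Element | Behind the 76% | Current primary analysis |
|---|---|---|
| Outcome | total intracranial volume | intra-parenchymal volume |
| Population | up to 8 hours | up to 3 hours, number not given |
| Scale | ml, SD 28 | log volume, SD and correlation not given |
| Missing scans | complete pairs only | patients with one scan kept |

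**4. Illustration on the planned scale.** Assumptions, not document figures: 50-80% of the 901 were randomised within 3 hours (450 to 721 paired patients); the ratio stays at 24/28, so the effect is ln(28/24) = 0.154 in size; the log-scale correlation is 0.6, so residual SD = 0.8 × log SD. A log SD of 0.83 follows if volumes are log-normal with SD equal to mean (28/28): √ln 2 = 0.833. The other values are for range only.

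| Log SD | Residual SD | 450 patients | 721 patients | all 901 |
|---|---|---|---|---|
| 0.83 | 0.67 | 69% | 87% | 93% |
| 1.0 | 0.80 | 53% | 73% | 82% |
| 1.2 | 0.96 | 40% | 58% | 67% |
| 1.5 | 1.20 | 28% | 41% | 49% |

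The results fall on both sides of 76%. With all 901, power equals 76% at a log SD of about 1.08. At a log SD of 0.83, about 531 patients (59% of 901) would still give 76%. The table leaves out any gain from patients with one scan, from the other covariates, or from a larger effect in the narrowed population.

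**5. Sample size.** Three totals appear: around 1700 (Sample size), about 1750 (Primary analysis) and up to 2,000 (Conclusion). The Sample size section calls about 1700 the feasible maximum, which does not fit with 2,000.

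**The case against.** A reader might infer that 76% is probably too high. The documents do not support that. The SAP narrowed the outcome and the time window because it expected dilution otherwise, so it implies a larger effect than 24/28. It adds covariates for precision and keeps patients whom the 901 excludes. Logging skewed volumes can itself raise power. The share within 3 hours is unknown, and the Introduction notes that recruitment was restricted to that window in 2016. A log SD of 1.5 has no source in the documents. All of this stands, and so no direction is claimed.

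A reader might also go further and remove patients with no intra-parenchymal blood from the count. No section says they leave the analysis.

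The SAP is open that it reuses the original inputs, says that the 95% ignores missing data, and lists its changes in the Conclusion. That limits the risk of misreading, but nowhere is the reader told that 76% does not apply to the current primary test. The paired-share conflict is small, about two percentage points at 50%, and the Sample size section itself speaks of around half. The differing totals are mainly a matter of wording.

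Finally, the size was set by feasibility and data collection was finished, so no estimate, interval or analysis set depends on the figure. That bears on how serious the point is, not on whether it holds.

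**Conclusion.** The point holds as an out-of-date power statement, not as an arithmetic error. The 95% and 76% are right for total volume in ml, up to 8 hours, with complete pairs. For the current primary analysis power is not given, and it cannot be derived from the document, because the number within 3 hours and the log-scale SD and correlation are not stated. Under the assumptions in the working, with 450 to 721 paired patients, it runs from about 28% to 87%. Separately, the SAP's statement that fewer than half had both scans puts even the old figure below 74%.

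The consequence is limited to how a null result is read. The point should be corrected, but it does not threaten the analysis.

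**What to change.** - Label the 95% and 76% as applying to the superseded outcome, population and scale.
- Add power, or the ratio detectable at a stated power, for the actual primary analysis. Use the counts randomised within 3 hours (pre-randomisation scan only, post-randomisation scan only, both) and the log-scale SD and pre/post correlation for intra-parenchymal volume, all pooled over arms.
- Say when this was computed relative to unblinding. The Trial status section dates unblinding to 31 May 2019 and places this third version after a report of 6 June 2019, so a calculation added now cannot be presented as planning done before unblinding.
- Reconcile 53% with fewer than half scanned twice, and give one sample size in place of 1700, 1750 and 2,000.

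The cost is about half a day on data already held, plus wording. No allocation data, extra recruitment or change of outcome or model is needed. The downside is that the stated power may become less favourable.
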